### Sample Size

On the basis of a small-sample clinical trial, the effectiveness rate of the treatment group was 80.77% [31]. Additionally, a previous randomized controlled double-blind clinical study had a response rate of 45% [33]. Using the PASS tool (version 21), with a significance level of .05 and a power of 0.9, the total sample size was calculated as 78 participants. Accounting for a 20% dropout rate, the required sample size was determined to be 94 patients, with 47 in each group.

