### Randomization and Blinding

The randomization sequence will be generated by the data manager. The patients will be randomly assigned to either the treatment group or the control group in a 1:1 ratio. Blinding methods will not be used in this clinical trial. Although blinding of participants is not feasible due to the nature of the intervention, the following blinding strategies will be implemented in the study design to minimize potential bias: health care providers administering the treatment, outcome assessors, and data analysts will all be kept blinded to group allocation. Specifically, the treatment providers responsible for assigning the interventions will not participate in subsequent efficacy or safety evaluations. During follow-up visits, clinical assessors will perform dermatological lesion observation and grading without knowledge of the participants’ group assignments. For the final statistical analysis, analysts will process data using anonymized codes, and blinding will only be lifted after the statistical analysis is completed. This approach was designed to ensure objectivity and accuracy in outcome evaluation and data interpretation.

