### Statistical Analysis

Data will be analyzed using SPSS Statistics for Windows (version 26.0; IBM Corp). Continuous data following a normal distribution will be expressed as means and SDs and compared within groups using a paired 2-tailed *t* test or between groups using an independent-sample 2-tailed *t* test. Data will be presented as frequencies and percentages, with chi-square tests for group comparisons and rank sum tests for ranked data. For continuous data that are not normally distributed, between-group comparisons will be performed using the Mann-Whitney *U* test, with data described as medians and IQRs. For measurements involving multiple time points, nonparametric methods such as the Friedman test will be used to ensure robust and reliable findings. A *P* value of <.05 will be considered statistically significant.

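### The 94 patients allow for about 17% dropout, not the stated 20%: the calculated 78 was multiplied by 1.20 instead of divided by 0.80

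*Protocol article*

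**What the plan says.** The Sample Size section of the protocol article gives every input and the result in one paragraph:

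- Treatment rate, from a small earlier trial: "the effectiveness rate of the treatment group was 80.77" per cent.
- Second rate, from another study: "a previous randomized controlled double-blind clinical study had a response rate of 45" per cent. The text does not call it the control rate, but no other rate is given for that purpose.
- Error rates: "with a significance level of .05 and a power of 0.9". Sidedness is not stated.
- Result before attrition: "the total sample size was calculated as 78 participants".
- Result after attrition: "Accounting for a 20% dropout rate, the required sample size was determined to be 94 patients, with 47 in each group".

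Under Randomization and Blinding, patients are "randomly assigned to either the treatment group or the control group in a 1:1 ratio", so 78 means 39 per group. For categorical outcomes the Statistical Analysis section provides for frequencies and percentages, "with chi-square tests for group comparisons and rank sum tests for ranked data". The total of 94 also appears in the Abstract and under Study Design.

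**The concern.** The paragraph gives a calculated need of 78, an expected loss of 20%, and 94 as the number that covers that loss. The natural reading is that 94 randomised patients, less 20%, leave 78 for analysis. They do not.

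At stake is the accuracy of figures that the results paper will carry forward. If dropout turns out exactly as planned, the trial will have about 75 evaluable patients against a stated need of 78. It would then appear to have fallen short, when the gap comes from the inflation step. The document also overstates how much attrition the design can absorb. The Withdrawal Criteria list several routes out of the study, including failure to complete treatment and observation for any reason, so the allowance may well be used.

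**Working it through.** **Inputs** (Sample Size section unless noted): calculated total N = 78, or 39 per group at 1:1 (Randomization and Blinding); dropout d = 0.20; stated total 94, or 47 per group.

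**1. Reproducing the stated figure.** Using N × (1 + d):

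- Total: 78 × 1.20 = 93.6, rounded up to 94.
- Per group: 39 × 1.20 = 46.8, rounded up to 47.

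Both printed numbers come out exactly, so this is evidently the step that was used.

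**2. The number that leaves 78 after 20% loss.** If a share d of those randomised is lost, N = n × (1 − d), so n = N / (1 − d):

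- Total: 78 / 0.80 = 97.5, rounded up to 98.
- Per group: 39 / 0.80 = 48.75, rounded up to 49.
- Check: 98 × 0.80 = 78.4, which is at least 78.

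The stated total is 98 − 94 = 4 patients lower.

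**3. What 94 delivers.**

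- At 20% dropout: 94 × 0.80 = 75.2, so about 75 evaluable (37.6 per group), 3 short of 78.
- Largest dropout that still leaves 78: 1 − 78/94 = 0.170, about 17%.

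**4. Effect on power.** Two assumptions are needed because the section states neither: that 45% is the control rate, and that the test is a two-sided 0.05 chi-square without continuity correction. Exact power comes from enumerating all pairs of binomial outcomes at 80.77% v 45%:

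| Evaluable (JDXZ + urea) | Exact power |
|---|---|
| 39 + 39 = 78 | 0.922 |
| 38 + 37 = 75 | 0.922 |
| 37 + 38 = 75 | 0.914 |
| 37 + 37 = 74 | 0.904 |

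On these assumptions the 0.90 target is still met at 75.

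**5. Whether 78 itself can be faulted.** The PASS procedure is not described, so several standard formulas were tried for two-sided 0.05 and power 0.90:

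| Method and rates | n per group | Total |
|---|---|---|
| Pooled z, uncorrected, 80.77% v 45% | 36.2, so 37 | 74 |
| Unpooled z, uncorrected, 80.77% v 45% | 33.1, so 34 | 68 |
| Unpooled z, continuity-corrected, 80.77% v 45% | 38.47, so 39 | 78 |
| Pooled z, uncorrected, 80% v 45% | 38.09, so 39 | 78 |

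Two ordinary routes return exactly 78. The base figure is therefore reproducible, though the document does not show which route was taken.

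**The case against.** The strongest reply is that this changes nothing of substance. The gap is about 3 evaluable patients in a trial that calls itself exploratory. Power at 75 stays above 0.90 under a plausible form of the planned test. The Results section reports 81 patients already enrolled on December 1, 2025. Adding 20% is also a common shorthand, and the text never says in so many words that 78 remain after the loss. All of this stands as an argument about consequence, and it is why no further recruitment is asked for. It does not make the sentence correct. The section speaks of a dropout rate and a required size, and for those terms 94 is the wrong number. Rounding cannot turn 97.5 into 94.

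A reader might go further in two directions that the document does not support:

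- **That 78 is itself wrong or too small.** It is true that an uncorrected pooled calculation at 80.77% v 45% gives 74. But two standard calculations give 78 exactly, and the Statistical Analysis section says only that chi-square tests will be used, without specifying a correction. The 78 cannot be faulted from what is printed.
- **That the dropout step costs the trial its 90% power.** Under the assumptions in the working it does not. A more conservative test might miss 0.90, but Fisher's exact test, for example, already falls below it at the full 39 + 39 (0.877), so that shortfall would not come from the dropout formula. The document does not plan that test either.

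**Conclusion.** The point holds as an arithmetic error in a stated design figure. Given 78 and 20%, the required number is 98, not 94. Given 94, the tolerable dropout is about 17%, and 20% dropout leaves about 75. This part needs only the printed numbers and the ordinary meaning of a dropout rate.

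The practical effect is minor: exact power of about 0.91 to 0.92 at 75 evaluable, against 0.92 at 78. That comparison rests on 45% being the control rate and on a two-sided 0.05 uncorrected chi-square test, neither of which the Sample Size section confirms. It is a correction to make before results are reported, and it gives no reason to doubt the design.

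**What to change.** Keep 94 and correct the sentence in the Sample Size section, for example: *78 evaluable participants are required; 94 randomised (47 per group) allows for about 17% dropout; at 20% dropout about 75 are evaluable.*

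In the same place, the authors should state the test, the sidedness and the rates actually entered in PASS, and say that 45% is the assumed control rate if that is so. Only they know what was entered, so no particular test should be written in on their behalf.

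The cost is one or two sentences. The 94 in the Abstract and under Study Design stays as it is, and no extra patients, time or change of analysis is needed. The only thing given up is a slightly more favourable claim about tolerable dropout.

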### Ethical Considerations

This RCT has received joint ethics approval from the institutional review boards of Shanxi Provincial Hospital of Traditional Chinese Medicine, Shanxi Cancer Hospital, and the Second Affiliated Hospital of Shanxi Medical University (approval 2024 KY-07026 and 2024KYY1-07014). Participants who sign the informed consent form will be enrolled in the study, with the right to withdraw at any point during the trial. Finally, the results of this RCT will be published in a relevant academic journal on completion of the trial irrespective of whether the RCT yields negative or positive outcomes. This study has been registered with the Chinese Clinical Trial Registry (ChiCTR2400086657).

### Trial Monitoring

Paper details will be managed by a designated individual and stored securely. Access to the e–medical case system will be restricted to authorized users. Before the commencement of the project, the researchers underwent rigorous training on the experimental protocol, and the uniformity of the quantitative metrics for symptoms and signs was meticulously verified. Any modifications to this protocol are subject to the prior approval of the ethics committee at Shanxi Provincial Hospital of Traditional Chinese Medicine to ensure the trial’s probity and adherence to ethical standards.

## Results

This study is currently underway. As of December 1, 2025, a total of 81 eligible participants had been enrolled, all of whom were assigned to groups following the randomization principle. Among them, 42 participants were allocated to the JDXZ group (with an additional 2 participants pending enrollment), and 39 to the control group. Based on the current progress, the estimated trial completion date has been extended to January 31, 2026.

## Discussion

Currently, the investigation into skin-related toxicities caused by EGFR-TKIs remains in the exploratory phase, with its findings yet to be fully substantiated, thereby necessitating further comprehensive research. EGFR-TKIs have the potential to elicit the aggregation of inflammatory cells within the context of normal skin. A study by Satoh et al [34] showed EGFR-TKIs’ synergy with skin *Bacillus* acnes to boost interleukin (IL)-36γ in keratinocytes. EGFR-TKIs suppressed *EGFR* signaling and upregulated KLF4, whereas *Bacillus* acnes triggered the activation of the nuclear factor kappa-light-chain-enhancer of activated B cells (NF-κB). KLF4 and NF-κB collaborate to upregulate IL-36γ promoter activity, thereby inducing neutrophil recruitment via IL-8 and worsening skin inflammation. EGFR-TKIs not only suppress the proliferative activity of basal keratinocytes but also facilitate their transition toward terminal differentiation, ultimately leading to xerosis of the skin. Erlotinib, as demonstrated by Ikarashi et al [35], markedly lowered aquaporin-3 expression in keratinocytes via the extracellular signal–regulated kinase pathway. Aquaporin-3 is crucial for skin hydration; reduced expression may impair this function. EGFR-TKIs have the potential to disrupt the intimate associations between basal keratinocytes, consequently impairing the epidermal barrier’s functionality. Gefitinib impairs the epidermal barrier by reducing claudin-1 and claudin-4 expression and increasing claudin-2 levels, as discovered by Fang et al [36].

Astragaloside IV, the main active compound of Astragalus, can inhibit the production of pro-inflammatory cytokines and the expression of TLR4 and its downstream signaling molecules, NF-κB, iNOS (inducible nitric oxide synthase), and COX-2 (cyclooxygenase-2) proteins [30]. *Astragalus* polysacharin, a monomeric *Astragalus* extract, curbs inflammatory cytokine (tumor necrosis factor, IL-6, and monocyte chemoattractant protein 1) production in lipopolysaccharide-activated RAW264.7 macrophages through NF-κB and mitogen-activated protein kinase (extracellular signal–regulated kinase and c-Jun N-terminal kinase) pathways [37]. Compounds 4 (3H) -quinazolinone (I) and 2,4 (1H, 3H) -quinazolindione (II) from purified *I indigotica Fort* effectively eliminate *S aureus*, *Escherichia coli*, *Bacillus subtilis*, and *Salmonella* [38]. Min et al [39] found that *I indigotica Fort* extract eases atopic dermatitis–like inflammation by suppressing NF-κB pathway–induced cytokine and chemokine production. Chymotrypsin severs desmosome links in skin keratinocytes, speeding cell shedding and boosting epithelial metabolism [40]. *C margaritifera*’s bioactives boost chymotrypsin, stimulate skin cell growth, and enhance collagen synthesis for skin regeneration and elasticity [40]. Reports confirm the synergistic effects of *A membranaceus*, *I indigotica Fort*, and *C margaritifera*, deeming JDXZ granules safe and effective for inflammation, antibacterial protection, and skin protection.

In the treatment of NSCLC with EGFR-TKIs, the presence of a rash has been shown to significantly predict the effectiveness of the treatment, particularly in patients with unknown *EGFR* mutation status [17]. As a result, clinicians must closely monitor skin toxicity throughout the entire course of treatment and manage it appropriately to prevent treatment discontinuation or dose reduction of EGFR-TKIs. Building on the clinical promise of JDXZ granules for EGFR-TKI-induced skin toxicity demonstrated in this RCT, a follow-up RCT is warranted to rigorously assess the treatment’s efficacy and safety, with the goals of reducing skin toxicity and enhancing patient quality of life. In this study, the severity of the rash will be graded according to the NCI-CTCAE 5.0 criteria. Assessment tools such as the itch numerical rating scale, the Dermatology Life Quality Index, and the European Organisation for Research and Treatment of Cancer Quality of Life Questionnaire Core 30 will be used. Additionally, serum levels of fibroblast growth factor 7 [41] and hepatocyte growth factor [42] will be incorporated as biomarkers, with WoMo [43,44] scores and dermatopathological findings serving as secondary end points. This approach provides a more comprehensive and updated perspective on EGFR-TKI–associated cutaneous toxicities.

However, this nonblinded study has limitations, first, in its level of evidence, with potential issues such as unevenly designed control groups and subjective bias in patient-reported outcomes (eg, itching and pain). Furthermore, the collection of long-term medication safety data remains insufficient. Should this study show promising signs, a more rigorously designed multicenter, large-sample, randomized, double-blind, double-dummy, active- or placebo-controlled clinical trial will be necessary for further validation. Such a step is critical to elevate the findings to a higher evidence level and support their potential inclusion in clinical guidelines. Future research should also focus on identifying predominant responders to JDXZ granules based on specific TCM syndrome types or biomarkers, enabling more precise application. Additionally, exploring synergistic effects with conventional Western treatments (such as topical corticosteroids or oral antibiotics) may help reduce the dosage and duration of antibiotic or corticosteroid use, thereby minimizing potential side effects.
